#### Quality of life

This will be assessed with the FIQR [32], a tool which tries to address the limitations of the Fibromyalgia Impact Questionnaire (FIQ) [33] while at the same time maintaining the basic properties of the FIQ. The FIQR is composed of 21 questions that make reference to the week prior to answering the questionnaire. Each question is based on an 11-point numeric rating scale of 0 to 10, with 10 being “worst”. The questionnaire is divided into three linked domains: Function, overall impact and symptoms. The “symptoms” domain contains four new questions relating to memory, tenderness, balance and environmental sensitivity (to loud noises, bright lights, odours and cold temperatures). The total FIQR score is the sum of the following 3 domain scores that can reach a maximum of 100 points: The “function” score (from 0 to 90) is divided by 3; the “overall impact” score (from 0 to 20) is not changed and the “symptoms” score (from 0 to 100) is divided by 2. Higher values indicate a poorer quality of life.

#### Quality of sleep

This will be evaluated with the Pittsburgh Sleep Qualitiy Index (PSQI) [34] a retrospective tool for measureing quality of sleep and sleep disorders. The PSQI is a 19-item questionnaire that refers to last month. It contains 7 sleep components: Subjective sleep quality, sleep latency, sleep duration, habitual sleep efficiency, sleep disturbances, use of sleeping medication and daytime dysfunction. The total PSQI is the sum of all component scores that can reach a maximum of 21 points. Higher values indicate a poorer sleep quality.

#### Fatigue

This will be evaluated by the Multidimensional Fatigue Inventory (MFI) [35], a 20-item assessment tool with five domains: General fatigue, physical fatigue, mental fatigue, reduced activity and reduced motivation. Each fatigue domain consists of four items and has a potential score ranging from 4 to 20, where higher MFI scores indicate a higher degree of fatigue.

#### Self-confidence in balance

This will be assessed with the Activities-specific Balance Confidence (ABC) scale [36], a 16-item questionnaire that measures the self-confidence in balance for performing ADL’s. Each item is based on a 0–100 scale where 0 is “no confidence” and 100 is “total confidence”. The total ABC score is calculated using the sum of all-items (range 0 to 1600) divided by 16. Scores >80% indicate a high level of physical functioning, 50–80% a moderate level, and scores <50% a low level of physical functioning. Scores <67% in older adults are predictive of future falls [37].

#### Physical ability

This will be measured with the 6-minute walk test [38], which determines the maximum distance that a person can walk in 6 minutes along a 20-m corridor. Heart rate (HR) and oxygen saturation will also be assessed with pulse oximetry. Dyspnea and lower limb fatigue will be measured with the modified Borg scale [39]. These parameters will be registered before the start of the test, immediately after and during recovery time (when the patient returns to baseline HR).

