**Methods/Design:**

The study protocol will be a single-blind randomised controlled trial. Forty women diagnosed with fibromyalgia will be randomly assigned into 2 groups: Aquatic Therapy (*n* = 20) or Land-based Therapy (*n* = 20). Both interventions include 60-min therapy sessions, structured into 4 sections: Warm-up, Proprioceptive Exercises, Stretching and Relaxation. These sessions will be carried out 3 times a week for 3 months. Primary outcomes are balance (static and dynamic) and pain (intensity and threshold). Secondary outcomes include functional balance, quality of life, quality of sleep, fatigue, self-confidence in balance and physical ability. Outcome measures will be evaluated at baseline, at the end of the 3-month intervention period, and 6-weeks post-treatment. Statistical analysis will be carried out using the SPSS 21.0 program for Windows and a significance level of *p* ≤ 0.05 will be used for all tests.

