### Statistical issues

#### Sample size calculation

The sample size was calculated to find a difference of ± 2.5 points between intervention groups on the VAS pain intensity scale [40], with a standard deviation of 2.5 points [41].

In order to achieve a statistical power of 80% with a significance level of *p* ≤ 0.05 and assuming a 20% dropout rate, an estimated 20 participants are required in each of the intervention groups. This sample size allows for detecting differences of 2 ± 2 s in the TUG test, with a statistical power of 80% and a significance level of *p* ≤ 0.05, assuming a 20% dropout rate.

The sample size was defined for a bilateral hypothesis and was carried out by the ENE software.

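### The recovery reading after the 6-minute walk is triggered by heart rate returning to its pre-walk value, so recovery heart rate is uninformative and the other three recovery readings share no common time

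*Protocol article*

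**What the plan says.** The Physical ability section of the protocol article measures this domain with the 6-minute walk test, which "determines the maximum distance that a person can walk in 6 minutes along a 20-m corridor". Four parameters accompany the distance: "Heart rate (HR) and oxygen saturation will also be assessed with pulse oximetry", and "Dyspnea and lower limb fatigue will be measured with the modified Borg scale".

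One timing rule covers all four. "These parameters will be registered before the start of the test", then "immediately after and during recovery time (when the patient returns to baseline HR". The article gives no clock time for the recovery reading and no margin within which HR counts as returned. It does not list the elapsed time among the parameters. No other section changes the rule.

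The abstract places the domain at secondary level: "Secondary outcomes include functional balance, quality of life, quality of sleep, fatigue, self-confidence in balance and physical ability". Under Procedures, patients are assessed at baseline, at the end of treatment and at 6 weeks, so the rule applies at three visits.

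**The concern.** A recovery measurement should show how far a patient has recovered by a given moment, or how long recovery takes. This rule does neither for HR. It waits until HR has reached a preset value and then records that value. For saturation, dyspnoea and leg fatigue, the waiting time depends on each patient's own HR recovery, so two patients may be read minutes apart.

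The trial compares two exercise programmes and means to attribute differences to the environment in which they are performed. If one programme speeds recovery after exertion, the recovery HR cannot show it, and the other three values cannot be set against elapsed time unless that time is also recorded.

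**Working it through.** The plan states no figure on this point, so the check is one of logic, followed by illustrations on assumed values.

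**1. Recovery HR.** Let B be pre-walk HR at a visit, T the time of the recovery reading, and d the tolerance for counting HR as back at baseline (not stated; d = 0 if exact). The rule sets T so that HR(T) = B + d. Hence HR(T) − B = d for every patient. The difference between arms in this quantity is d − d = 0, and so is the change between visits. If training shifts B itself, recovery HR shifts with it, but that only repeats the pre-walk reading.

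**2. How many readings are affected.** Per visit there are 4 parameters × 3 moments = 12 readings. One (recovery HR) is fixed by the rule. Three (recovery saturation, dyspnoea, fatigue) have no common time. The remaining 4 × 2 = 8, and the walk distance, are unaffected.

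**3. How far reading times could spread.** The document gives no HR data, so all inputs here are assumptions: B with mean 78 bpm (SD 9), rise R at the end of the walk with mean 35 bpm (SD 10, floored at 8), and exponential recovery HR(t) = B + R·exp(−t/τ), with τ log-normal, median 60 or 90 s, log-SD 0.4. Then T = τ·ln(R/d). For one patient with R = 35 and d = 3, ln(35/3) = 2.457, so T = 60 × 2.457 = 147 s or 90 × 2.457 = 221 s. Simulating 20,000 patients per setting gives:

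| d (bpm) | median τ (s) | T: 5th / 50th / 95th percentile (s) | SD of HR(T) − B |
|---|---|---|---|
| 1 | 60 | 106 / 210 / 410 | 0.0 |
| 1 | 90 | 159 / 316 / 615 | 0.0 |
| 3 | 60 | 71 / 144 / 286 | 0.0 |
| 3 | 90 | 106 / 215 / 430 | 0.0 |
| 5 | 60 | 53 / 113 / 228 | 0.0 |
| 5 | 90 | 79 / 169 / 343 | 0.0 |

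Across settings, the 5th to 95th percentiles run from 53 to 615 s.

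**4. What other readings would show.** Under the same assumptions, HR above baseline at a fixed 60 s averages 12.9 bpm (SD 6.2) for τ = 60 s and 17.6 to 17.7 bpm (SD 6.9 to 7.0) for τ = 90 s, a contrast of 17.6 − 12.9 = 4.7 to 17.7 − 12.9 = 4.8 bpm. Median time to return at d = 3 differs by 215 − 144 = 71 s. The triggered HR shows a contrast of 0.

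**5. Direction of any bias in the symptom readings.** Take two patients with equal peak symptoms, back at baseline HR after 2 and 10 min (assumed).
- If symptoms halve every 2 min in both, the shares remaining are 0.5^(2/2) = 50% and 0.5^(10/2) = 3.1%, a gap of 46.9 points that makes the slower recoverer look better.
- If symptom half-life scales with HR recovery (0.4 and 2 min), the shares are 0.5^(2/0.4) = 3.1% and 0.5^(10/2) = 3.1%, a gap of 0.

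If the slower patient's symptoms lag further behind HR, or start from a higher peak, the sign can reverse. The document supplies nothing to choose between these cases.

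**The case against.** The strongest reply is that nothing in the trial turns on these readings. No hypothesis names them. The sample size rests on a "difference of ± 2.5 points between intervention groups on the VAS pain intensity scale", with a second calculation for the Timed Up & Go test. This stands, and it limits the weight of the point.

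A second reply is that sampling at an equal state of HR recovery is a legitimate design. That stands for saturation, dyspnoea and fatigue, which remain interpretable on those terms. It does not help HR, the variable that defines the state.

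Third, the recovery phrase might define a period that assessors do time, and a condensed article may leave tolerance, maximum wait and timing to the full protocol. The parenthesis ties the reading to the return to baseline, and the looser reading still fixes no common time. The full protocol may well time the return. The point therefore rests on the sampling rule that the article states, and the missing operational detail is not counted against it.

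Two stronger readings are tempting. A reader might infer that symptom and saturation readings are biased against the arm whose fitness improves more. That needs symptom recovery to be unrelated to HR recovery, which the document does not say. A reader might also infer that the least fit patients will lack a recovery reading. The document gives no HR data, visit length or cut-off, and its silence on patients whose HR does not return is not evidence that they go unrecorded.

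**Conclusion.** The point holds, and it is minor. That recovery HR repeats pre-walk HR follows from the stated rule and needs no assumption beyond a common tolerance. That the other three recovery readings lack a common time also follows from the rule; only the size of the spread (53 to 615 s in the illustration) depends on assumed values. A faster recovery is not captured by the parameters the article lists. Neither a direction of bias nor selective missingness can be concluded. The effect is confined to ancillary readings within a secondary outcome, and the primary outcomes are not involved.

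**What to change.** At every visit, register HR, saturation, dyspnoea and leg fatigue at one fixed time after the walk ends, the same for all patients (for example 1 or 2 min). Analyse the HR fall from the end of the test to that time. Also record the time until HR is back at its pre-walk value, within a stated tolerance, and censor it at a fixed limit. If the full protocol already times the return, say so and name it as a registered parameter.

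The cost is a sentence or two in the assessment procedure and a stopwatch, with the same oximeter, scale and assessor. There is a small downside: one more timed reading, and assessors still wait for the return to baseline up to the limit.

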### Interventions

The interventions designed in this protocol consist of two similar physiotherapy protocols for people with FM. Both will include 60-min sessions that will be carried out 3 times a week for 3 months by a physiotherapist, in groups of 8–9 people maximum.

Both interventions will be based on: 15 min of warm-up, 25 min of proprioceptive exercises, 8 min of stretching and 12 min of relaxation.

For adequate training of balance and postural control, patients will be required to contract their local musculature (“core stability”) before starting any specific exercise. The transversus abdominis, pelvic floor muscles, internal oblique and multifidus form the local musculature. The most important aspect of achieving core stability will be co-activation of the first two muscles, for which patients will have to place their pelvis in a neutral position. Before starting the interventions, patients will receive anatomy and palpation classes to aid in identification of the involved musculature and how its contraction is perceived.

The protocols have been created by the main researcher based on available scientific evidence. The protocols were designed with the intention of being as similar as possible in order to attribute any statistically significant difference in outcomes between the two groups to the environment where the interventions were performed. Sessions will be pre-programmed with a progression in difficulty over the intervention period: Shorter pauses, higher exercise intensity, eyes closed, etc.

Patients will not be allowed to begin any other activity during the study period. They will have to report any problems, whether event-related or not, as well as any medication changes.

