### Statistical analysis

Analysis will be descriptive of all outcomes included in the study, expressing quantitative outcomes with their mean ± standard deviation and qualitative outcomes with their absolute value, percentage and 95% confidence intervals.

The association between qualitative outcomes will be studied using the Chi-square test. After checking normality with the Kolmogorov-Smirnov test, the Student *T* test or the Mann–Whitney *U* test will be used to perform mean comparison. The mean comparison between two or more categories will be studied with the ANOVA test or Kruskal-Wallis test, as appropriate.

The correlation between quantitative outcomes will be analysed with the Pearson or Spearman correlation coefficients, as appropriate.

The mean comparisons for related outcomes in two different moments will be studied with the Wilcoxon test. Friedman test will be used when comparing more than two moments. In addition, the clinical relevance of the intervention will be studied by calculating the relative risk, relative risk reduction, absolute risk reduction and the number needed to treat. All of these measures will be presented with their 95% confidence interval.

A multivariate analysis by multiple linear regression or logistic regression to adjust for the effectiveness of the intervention according to possible confounding factors and to determine what other outcomes might be associated with each result will be carried out. Only the outcomes that show a statistical significance p <0.20 in the bivariate analysis, will be included in the multivariate regression analysis. In addition, a stepwise backward modelling strategy will be carried out.

All analysis will be done by intention to treat [42], where the total value of randomisation is preserved and control of any counfounders’ effect is insured.

The significance level set for all the analysis will be *p* ≤0.05. The SPSS statistical software, version 21.0 (SPSS, Chicago, IL) will be used for all analysis.

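### Therapy is delivered in classes, but the sample size and the between-arm tests treat patients as independent; if outcomes correlate within classes, the type I error exceeds 5%

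*Protocol article*

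**What the plan says.** Patients are randomised individually, 1:1, to 20 per arm (Randomisation). Each arm then has 60-minute sessions three times a week for three months, led by a physiotherapist and held "in groups of 8–9 people maximum" (Interventions). Tables 2 and 3 include joint activity: relay races and group ball-catching in both arms, and a shared mat exercise in the water arm.

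Under Sample size calculation the text reads "The sample size was calculated to find a difference of ± 2.5 points between intervention groups on the VAS pain intensity scale", "with a standard deviation of 2.5 points". With 80% power, a two-sided 0.05 level and 20% dropout, the result is that "an estimated 20 participants are required in each of the intervention groups". The same number is said to serve a Timed Up & Go (TUG) difference of 2 s with an SD of 2 s. No design effect or ICC appears.

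Under Statistical analysis, the Student t or Mann–Whitney test "will be used to perform mean comparison". ANOVA, Kruskal-Wallis, chi-square and ordinary linear or logistic regression are also named. Wilcoxon and Friedman deal with repeated measures within a patient. None of these methods has a term for class.

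**The concern.** Women in one class share sessions, peers and pace for three months, so their outcomes may resemble each other more than those of women in different classes. The two arms never share a class. Differences between classes therefore feed directly into the difference between arms. A test that counts patients as independent leaves this variation out of its standard error and rejects too often.

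This matters for the trial's stated aim. Interventions says the two programmes were made as alike as possible so that a significant difference can be put down to the environment. With about three classes per arm, chance differences between classes are a rival explanation that the planned tests cannot separate from water versus land.

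**Working it through.** **Inputs from the document.** Difference 2.5 and SD 2.5 (TUG: 2 and 2), so the standardised difference is 1.0 for both; two-sided 0.05; power 80%; dropout 20%; class size at most 8–9.

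**Assumed input.** ICC of 0.01, 0.05 or 0.10. The document gives none.

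**1. The plan's own figure.** n per arm = 2 × (1.960 + 0.842)² / 1.0² = 15.7, rounded up to 16. Then 16 / 0.8 = 20. This reproduces the stated 20 exactly, so the design effect was implicitly 1. By the t-test, power is 78% with 16 per arm and 87% with 20. The gap between 78% and 80% comes from the normal formula and has nothing to do with classes.

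**2. Number of classes.** 20 / 9 = 2.2 and 20 / 8 = 2.5, so at least three per arm. I use classes of 7, 7 and 6 with all 20 measured, and 6, 5 and 5 with 16 completers.

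**3. Variance inflation.** Design effect (DE) = 1 + (m − 1) × ICC, with m = sum(size²) / sum(size).
- 16 completers: m = (36 + 25 + 25) / 16 = 5.375; DE = 1.044, 1.219, 1.438.
- 20 measured: m = (49 + 49 + 36) / 20 = 6.7; DE = 1.057, 1.285, 1.570.

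**4. Type I error of the unadjusted test.** The approximation is 2 × [1 − Φ(1.96 / √DE)]. The planned t-test was also simulated in several runs, and the ranges below cover them.

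| ICC | 16 per arm, formula | 16 per arm, simulated | 20 per arm, formula | 20 per arm, simulated |
|---|---|---|---|---|
| 0.01 | 5.5% | 5.5–5.6% | 5.7% | 5.6–5.8% |
| 0.05 | 7.6% | 7.5–7.7% | 8.4% | 8.4–8.7% |
| 0.10 | 10.2% | 10.4% | 11.8% | 12.0% |

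Full retention does not cure the inflation. It makes it slightly worse, because the classes are larger.

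**5. Power at a standardised difference of 1.0, 16 completers per arm (simulated).**

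| ICC | Planned t-test | t-test on class means (3 + 3 − 2 = 4 df) |
|---|---|---|
| 0 | 78% | 57% |
| 0.01 | 78% | 55% |
| 0.05 | 76–77% | 49% |
| 0.10 | 75% | 44% |

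The planned test loses little power of its own. The cost appears when class is properly accounted for.

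**The case against.** The strongest reply is that nothing shows the ICC to be other than negligible. Patients are randomised individually. Sessions are pre-programmed, every class in an arm follows one scripted table at one venue, and blinded assessors measure outcomes individually at a separate visit. The text does not say that different physiotherapists lead different classes, or that class membership is fixed. At an ICC of 0.01 the type I error is about 5.5%, which is trivial. A class-level sensitivity model could also sit in an analysis plan that is not shown.

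Most of this stands as a limit on size. It rules out the flat statement, which a reader might infer, that the power is overstated and the p-values are too small. Both depend on a positive within-class correlation that the document neither gives nor excludes. It does not remove the point: the article names its tests and sample-size inputs, and these assume independence while the same article describes group delivery.

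A second tempting reading is that power really drops to about 69% at an ICC of 0.05, found by putting 16 / 1.219 = 13.1 per arm into a t-test. That figure describes neither relevant test. The planned test keeps 76–77%, and a test on class means with 4 df has about 49%.

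It would also go too far to say there is no reserve at all. With all 20 per arm measured, t-test power is 87% with no clustering. That reserve protects power, not the type I error.

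**Conclusion.** The point holds in conditional form. Delivery in at least three classes per arm is ignored by both the sample size and all named between-arm tests. If outcomes are positively correlated within classes, the planned t-test rejects a true null more often than 5%. The excess is negligible at an ICC of 0.01 and material at 0.05 to 0.10, where the error is roughly one and a half times to more than twice nominal. The result rests on the assumed ICC range, on stable membership of three near-equal classes per arm, and on normally distributed outcomes. The main consequence is a higher risk of a false environment effect. A large loss of power in the analysis as planned is not supported.

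**What to change.** Leave enrolment as it is.

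- Record each patient's class (and any change of class) while sessions run.
- Keep the planned comparison. Prespecify a sensitivity analysis of the primary outcomes that accounts for class with a small-sample correction, for example a class random effect with Satterthwaite degrees of freedom. Report the ICC with its interval. With about six classes, this model is better not made primary.
- Read a significant difference as an effect of environment only with that analysis alongside.
- Restate the power as about 78% by the t-test at 16 completers per arm (87% if all 20 are measured), assuming no within-class correlation. Add that a class-adjusted analysis has less: a test on class means (4 df) has about 49% at an assumed ICC of 0.05 with 16 completers.

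The cost is one recorded variable, one additional model and a less favourable power statement. With about six classes the adjusted interval will be wide and the ICC imprecise, so the sensitivity analysis may fail to confirm a real difference.

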### Aquatic therapy

The twenty patients included in the EG will perform aquatic therapy in the Rialta Sports Complex, in A Coruña (Spain). The water temperature is 30 °C, with less than 1 °C of variation, and the environmental temperature is 27.5 °C, with less than 1 °C of variation. Sessions will be given in a swimming-pool of 20 × 6 m, with a 120-cm depth. The aquatic therapy protocol is described in Table 2.

**Table 2 Tab2:** Description of aquatic therapy protocol

Exercise blocks	Exercise descriptions	Repetitions/Action/Pause
Warm-up (15 min)	1. Running in water: With water at waist level, patients will run along the bottom of the pool, changing trajectory. 2. Can-Can kicks: Submerged to chest depth, patients will kick the water with alterating legs. 3. Hydro-Jumps: With feet on the pool’s floor, patients will jump, bending their knees at the highest point in their jump. 4. Pedaling: With a pool noodle under the neck, patients will move their legs in the motion of pedaling a bicycle while moving along the pool. 5. Rocking Horse: With one foot before the other, patients will alternate jumps with the front and back leg. 6. Relay Race: 2 groups. The winner will be the group that returns the baton to the first participant in the shortest time.	1. 3 min uninterrupted activity. 2. 3/30 s/15 s. 3. 3/30 s/15 s. 4. 3 min uninterrupted activity. 5. 3/30 s/15 s. 6. 2/1 min/20 s.
Proprioceptive exercises (25 min)	1. Playing Catch: In a group, patients will be sitting on a pool noddle and will have to maintain balance while throwing and catching the ball.	1. 3 min uninterrupted activity.
	2. Balance over pool noodles: Patients will be sitting on a pool noodle with hips and knees bent 90° and will have to keep balance in 3 different positions: a. With arms submerged and 90° abduction; b. one arm out of water and the other under water; c. from the initial position, they will have to do a trunk extension with shoulder extension, hip extension, knees pointing to the pool’s floor and neck extension.	2. 2 (for each position)/1 min/20 s.
	3. Turbulence standing: Standing, with water at the level of the chest and arms along the body; patients will have to do quick and short flexion/extension movements with the ULs generating significant turbulence. A good activation of local musculature will be essential for avoiding imbalance.	3. 4/15 s/15 s.

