	4. Exercises with kickboard: a. Patients will be sitting on a kickboard, with water at the height of neck. They will have to keep afloat with only the aid of pedaling and without moving along the pool. b. With one foot on the kickboard and the other on the pool’s floor, patients will have to lower the kickboard and place it 10 cm above the pool’s floor. They will have to maintain this position and move the kickboard forward, backward and sideways without allowing it to go to the water’s surface. The exercise will be done with both LLs, first placing the kickboard vertically and then horizontally.	4. a. 2/1 min/20 s.; b. 2/40 s/15 s.
	5. Double pool noodle: Patients will be standing with a pool noodle in each hand. They will have to submerge them in the water while raising knees to chest.	5. 3/50 s/20 s.
	6. The boat: 2 groups. Patients will have to submerge a large mat while maintaining a standing position with different supports: Double, single-leg and tandem.	6. 3 min uninterrupted activity.
Stretching (8 min)	Gastrocnemius, quadriceps, ischiotibial, adductors, quadratus lumborum, deltoid, triceps brachii, superior trapezius.	2 (right and left side)/30 seg/5 seg.
Relaxation (12 min)	An Ai-Chi sequence with music. 6 movements of the 19 that comprise the Ai-Chi done in the following order: “Folding”, “Soothing”, “Gathering”, “Freeing”, “Shifting” and “Accepting”.	12 min uninterrupted activity.

*ULs* upper limbs, *LLs* lower limbs

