### Land-based therapy

The twenty patients included in the CG will perform the intervention in one of the laboratories at the Faculty of Physical Therapy. The land-based therapy protocol is described in Table 3.

**Table 3 Tab3:** Description of land-based therapy protocol

Exercise blocks	Exercise descriptions	Repetitions/Action/Pause
Warm-up (15 min)	1. Vigorous Walking: Patients will have to walk forwards, backwards, snaking and changing direction energetically. 2. Standing exercises: a. On one leg, with an UL and its contralateral LL, patients will do a simultaneous abduction followed by addution. b. The shoulder flexion movement is combined with contralateral knee elevation. c. Patients will perform jumping jacks. 3. Ball Jumps: Patients will be sitting on a Bobath ball and will have to jump. 4. Pedaling: Patients will be positioned face up, with the hips and knees bent 90° and will have to do a pedaling motion with their legs, keeping the pelvis in a neutral position. 5. Relay Race: 2 groups. The winner will be the group that return the baton to the first participant in the shortest time.	1. 3 min of uninterrupted activity. 2. a. and b. 6 (3 for each diagonal)/15 s/5 s; c. 3/20 s/10 s. 3. 3/45 s/20 s. 4. 3/45 s/20 s. 5. 3/1 min/20 s.
Proprioceptive exercises (25 min)	1. Playing Catch: Patients will be placed in a circle and sitting on a Bobath ball. With single-foot support, they will have to maintain a good position while throwing and catching the ball.	1. 3 min of uninterrupted activity.
	2. The bridge: a. Patients will be positioned face up on a mat, with arms along the body and feet on a Bobath ball. They will have to raise their buttocks off the floor and hold this position (the bridge). b. Starting from the previous position, patients will do the bridge raising one of the LL supported on the ball together with the contralateral UL at the same time.	2. a. 2/1 min/20 s.; b. 4 (2 for each diagonal)/40 s/5 s.
	3. The knight: With one knee on a Dynair and the contralateral foot on a hedgehog (Erizo Senso® Balance), patients will have to maintain the position without losing balance.	3. 6 (3 for each side)/30 s/10 s.
	4. Standing balance: Standing on a Dynair, patients will have to maintain their balance while moving their center of gravity forward, backward and sideways. There can not be any contact with the floor through the Dynair. The exercise will also be performed on one leg.	4. 3/1 min/15 s.

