	5. Superman: On all fours, with hands holding a roll (SISSEL® Pilates Roller), patients will have to perform and hold the superman position (simultaneous extension of an UL and contralateral LL). The exercise will also be performed dynamically: Hand touching the knee and then moving away, while keeping the pelvis in a neutral position.	5. 8 (4 for each diagonal: 2 dynamic and 2 keeping the position)/30 s/10 s.
	6. Exercises with the roll (SISSEL® Pilates Roller): a. Patients will be sitting on one of the roll’s ends and must move their trunk backward (reaching the stability limit), while keeping both feet fully supported on the floor. b. With the spine resting on the roll and hands and feet on the floor, patients will place their hips and knees in a flexion of 90°, without losing balance. This exercise will also be performed dynamically (raising and lowering the legs) and removing one of the hand supports.	6. a. 3/15 s/10 s.; b. 4 (2 dynamic y 2 keeping the position)/50 s/10 s.
Stretching (8 min)	Gastrocnemius, quadriceps, ischiotibial, adductors, quadratus lumborum, deltoid, triceps brachii, superior trapezius.	2 (right and left side)/30 s/5 s.
Relaxation (12 min)	Jacobson Progressive muscle relaxation, with classical music.	12 min of uninterrupted activity.

*UL* upper limb, *LL* lower limb, *Dynair* Balance Soft Disc

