## Discussion

The main objective of this randomised controlled trial is to determine the effectiveness of two physiotherapy protocols in improving balance and decreasing pain in women with FM, at the end of the intervention and at 6-weeks follow-up. With the study conclusion, we expect to test the following null hypothesis: “There is no difference in balance or pain for participants undergoing physiotherapy interventions on land or in water”. The balance disorder observed in FM is a sympton that has been discovered only recently. This is why there are very few publications regarding. Specifically, in the MEDLINE database, we were able to identify only 11 randomized controlled trials that included physical interventions and balance improvement was included in their objectives. Of these 11 clinical trials, only three included physiotherapy as a treatment method [43–45]. Given this, we expect the study conclusion to contribute to the fund of scientific knowledge, providing evidence that physiotherapy is a safe and effective tool in the management of FM symptoms, specifically balance disorders and pain.

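### Any significant difference is to be credited to water, but the arms also differ in relaxation method and most proprioceptive exercises, so only the two programmes can be compared

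*Protocol article*

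**What the plan says.** The Interventions section of the protocol article calls the arms two similar protocols. It says they were meant to be as alike as possible "in order to attribute any statistically significant difference in outcomes between the two groups to the environment where the interventions were performed".

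The frame is the same in both arms: "Both will include 60-min sessions that will be carried out 3 times a week for 3 months by a physiotherapist", with each session divided into "15 min of warm-up, 25 min of proprioceptive exercises, 8 min of stretching and 12 min of relaxation".

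The content of the blocks is given in Table 2 (Aquatic therapy) and Table 3 (Land-based therapy). For relaxation, the aquatic arm has "An Ai-Chi sequence with music. 6 movements of the 19 that comprise the Ai-Chi", while the land arm has "Jacobson Progressive muscle relaxation, with classical music". In the proprioceptive block the second item, for example, is noodle balance in water ("Patients will be sitting on a pool noodle with hips and knees bent 90" degrees) and the bridge on land ("Patients will be positioned face up on a mat, with arms along the body and feet on a Bobath ball").

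The null hypothesis in the Discussion is set at programme level: "There is no difference in balance or pain for participants undergoing physiotherapy interventions on land or in water". The main objective at the end of the Background likewise concerns the effectiveness of two physiotherapy protocols.

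**The concern.** Crediting a difference to the environment requires the arms to differ in nothing else that could move the outcomes. Here the treatment content changes along with the medium. A significant result could come from water, from Ai-Chi rather than Jacobson relaxation, or from the choice of balance tasks.

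The content differences sit close to the primary outcomes. Balance is what the proprioceptive block is meant to train, and relaxation is a plausible route to pain.

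The Background presents the role of the environment as unsettled: German and Israeli guidelines favour water, while EULAR holds that the benefit of exercise does not depend on where it is done. A positive result labelled as an effect of the environment would be read as evidence on that question, which this design cannot supply.

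**Working it through.** **1. The plan's own session structure.** Stated blocks: 15 + 25 + 8 + 12 = 60 min in both arms. This adds up.

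**2. Tables 2 and 3 side by side.**

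| Block | Aquatic | Land | Match |
|---|---|---|---|
| Warm-up, 15 min | Running, can-can kicks, hydro-jumps, pedaling, rocking horse, relay race | Vigorous walking, standing diagonals and jumping jacks, ball jumps, pedaling, relay race | Partial: pedaling and relay race in both; running is close to walking |
| Proprioceptive, 25 min | Playing Catch, noodle balance, turbulence standing, kickboard, double noodle, The Boat | Playing Catch, the bridge, the knight, Standing Balance on a Dynair, superman, roll exercises | 1 of 6 items (Playing Catch, 3 min), on a noodle versus a Bobath ball with single-foot support |
| Stretching, 8 min | Eight muscle groups, 2 repetitions of 30 s | Same | Full |
| Relaxation, 12 min | Ai-Chi | Jacobson | None |

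**3. Share of session time with different content.** The warm-up and Playing Catch are counted as matched throughout.

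- Relaxation only: 12 / 60 = 20%.
- Adding the proprioceptive block less Playing Catch: 25 − 3 = 22; 22 + 12 = 34; 34 / 60 = 57%.
- Accepting The Boat (3 min) and Standing Balance (3 × 1 min of action) as counterparts: 22 − 3 = 19; 19 + 12 = 31; 31 / 60 = 52%.

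**4. Link to the outcome tests.** Static balance is measured by Romberg's test, standing with feet together and in tandem. Four of the six aquatic items include a standing task (turbulence, kickboard part b, double noodle, The Boat), and The Boat names tandem support. On land only Standing Balance is done standing, and no item names tandem. The arms therefore also differ in practice of the tested postures. Tandem stance is possible on land, as the test itself shows, so water does not force this difference.

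**5. Whether analysis can separate the two.** Let A = 1 for the aquatic arm and 0 for land, M the medium and C the content. Every participant has M = C = A, so

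E(Y) = α + β_M·M + β_C·C = α + (β_M + β_C)·A.

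Only the sum β_M + β_C can be estimated. The regression adjustment in the Statistical analysis section handles patient characteristics; it cannot split two factors that coincide in everyone.

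**The case against.** The strongest reply is that the sentence states an intention. It explains why the arms were matched, and the article contains no analysis rule or reporting commitment that assigns effects to water. The objective and null hypothesis are already at programme level.

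The matching is also substantial: the same session length, frequency, duration, block lengths and group-size cap, the same core-activation requirement, preparatory classes and planned progression, and identical stretching. Several water tasks work through buoyancy or resistance, so the environment might reasonably be taken to include the exercises it allows.

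Finally, the 52% and 57% depend on the pairing rule. Kickboard part b resembles Standing Balance at least as well as The Boat does, and some warm-up items counted as matched have no land counterpart.

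Much of this is right, but it does not rescue the attribution. The sentence gives the inferential purpose of the design, and the tables in the same article show that the design cannot serve it. That some tasks cannot be copied on land explains the confounding without removing it, and nothing in the article says the medium requires a different relaxation technique. The programme-level objective and null hypothesis show that this sentence goes further than the rest of the protocol. The point about pairing stands for the larger shares, which should be read as approximate; it leaves the 12 minutes of relaxation untouched.

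**Conclusion.** The concern holds. Medium and content are completely confounded by arm, so the trial can estimate the effect of the aquatic programme against the land-based programme but not the effect of water.

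The clear part of the difference is the relaxation block, one fifth of the session. Slightly more than half the session differs if proprioceptive items are matched largely by name and the warm-up is treated as equivalent. These shares describe content, not dose, and neither the size nor the direction of any effect on balance or pain can be worked out from the article.

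Randomisation, outcomes, sample size and the validity of the between-programme comparison are unaffected. Only the causal label is unsupported.

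**What to change.** In the Interventions section, replace the attribution to the environment with wording such as: *any difference in outcomes between the groups will be interpreted as the difference between the aquatic and the land-based programme as delivered*. Use the same wording when results are reported.

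This changes text only. The price is a narrower causal claim, which is the one the design supports.
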